**Neonatal**	
Early neonatal death (defined as a death within 7 days after delivery)	
Late neonatal death (defined as a death beyond 7 days and before 28 days after delivery)	
Early neonatal death (defined as a death within 7 days after delivery excluding those secondary to congenital anomalies)	
Late neonatal death (defined as a death beyond 7 days and before 28 days after delivery excluding those secondary to congenital anomalies)	
Birth weight adjusted for gestational age and sex	
Small for gestational age (< 10th centile)	
Advanced resuscitation at birth (assisted ventilation and/or drug administration and/or cardiac compressions)	
Admission to specialist care (SCBU/NICU/HDU/transitional care)	
Length of stay in each additional specialist care setting	
Suspected sepsis (clinically diagnosed defined as commenced on intravenous antibiotics for > 48 h after birth)	
Confirmed sepsis (positive microbiology)	
Brain injury (defined as any intraventricular haemorrhage (IVH) (excludes subependymal haemorrhages), parenchymal cystic or haemorrhagic lesion or persistent ventriculomegaly (VI > 97th percentile)	
Respiratory support (ventilation/CPAP)	
Days on respiratory support	
Supplementary oxygen requirements at 36 weeks corrected gestational age	
Necrotising enterocolitis (Bell’s stage 2 or 3)	
Retinopathy of prematurity requiring laser treatment	
Disabilities	
Congenital abnormalities	
Serious adverse events	

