### Outcome measures

The primary outcome is pregnancy loss defined as miscarriage, termination of pregnancy and perinatal mortality defined as stillbirth and neonatal death in the first week after birth. Secondary outcomes are detailed in Table 2. All the core outcomes for PTB are included [17].

**Table 2 Tab2:** Full description of all secondary outcomes including complete core outcome set for preterm birth

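### The retinopathy outcome is tied to laser, so a baby whose retinopathy needed treatment but was treated another way is counted as event-free

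*Protocol article*

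**What the plan says.** The neonatal part of Table 2 (Outcome measures) lists the eye outcome as "Retinopathy of prematurity requiring laser treatment". It names no disease stage and no other treatment, and no other part of the article widens the row.

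Two features of the table bear on how to read it:

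- Its caption presents it as a "Full description of all secondary outcomes including complete core outcome set for preterm birth". Within the table, only the 2-year row sends the reader to the statistical analysis plan for more detail.
- The bowel outcome in the same list is defined by severity of disease: "Necrotising enterocolitis (Bell’s stage 2 or 3)". It does not depend on which treatment was given.

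Under Statistical analysis, binary secondary outcomes are handled like the primary outcome, that is, by a log-binomial relative risk adjusted for the minimisation variables. The Trial status section says that recruitment opened on 1 February 2019 and that the article reflects protocol version 3.0 of 31 January 2020.

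**The concern.** A threshold of disease severe enough to need treatment is a sensible way to define this outcome. The difficulty is that the row sets the threshold by one treatment. Two babies with equally severe disease would be scored differently if one had laser and the other had something else: the first is an event, the second is not.

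The trial aims to improve outcomes for babies as well as mothers, so neonatal morbidity is part of how the result will be judged. Events of this kind will be few, and a definition that discards some of them makes a weak comparison weaker. If the choice of treatment also differed between the arms, the relative risk itself would shift.

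**Working it through.** **The plan's own figure.** The only design calculation is the sample size: 60% v 40% pregnancy loss, 90% power, alpha 0.05 (taken as two-sided), 1:1 allocation.

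n per arm = [1.96 × √(2 × 0.5 × 0.5) + 1.2816 × √(0.6 × 0.4 + 0.4 × 0.6)]² / 0.20² = (1.386 + 0.888)² / 0.04 ≈ 129.3, so 130 per arm and 260 in total, with power 0.902. The stated figure reproduces. The eye outcome plays no part in it.

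**Babies available for the comparison.** At the design rates, those who escape the primary outcome number:

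- ECC: 130 × 0.60 = 78
- expectant management: 130 × 0.40 = 52

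These are rough denominators. The primary outcome counts neonatal death only in the first week, and not every surviving baby will be born early enough to be at risk of retinopathy.

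**Effect of the laser condition.** Let f be the share of treated babies whose treatment was not laser. Then:

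counted RR = true RR × (1 − f in ECC) / (1 − f in expectant)

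The article gives no retinopathy rate and no value of f, so everything below is an assumption chosen to show the range. Take treated disease in 8% of ECC babies and 12% of expectant babies, a true RR of 0.08/0.12 = 0.67. Expected events are 78 × 0.08 = 6.2 and 52 × 0.12 = 6.2.

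| f in ECC | f in expectant | Counted RR |
|---|---|---|
| 0 | 0 | 0.67 |
| 0.30 | 0.30 | 0.08 × 0.70 / (0.12 × 0.70) = 0.67 |
| 0.20 | 0.40 | 0.08 × 0.80 / (0.12 × 0.60) = 0.89 |
| 0.25 | 0.50 | 0.08 × 0.75 / (0.12 × 0.50) = 1.00 |
| 0.40 | 0.20 | 0.08 × 0.60 / (0.12 × 0.80) = 0.50 |

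Equal shares leave the RR alone. Unequal shares move it, in either direction. The article gives no ground for choosing among the unequal rows.

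**Precision lost with equal shares.** Unadjusted SE of log RR = √(1/a − 1/78 + 1/b − 1/52), where a and b are the events in each arm.

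- All treated disease counted, a = b = 6.24: SE = 0.537, so the 95% interval around 0.67 is 0.23 to 1.91.
- 30% lost, a = b = 6.24 × 0.70 = 4.37: SE = 0.653, interval 0.19 to 2.40.

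**Power lost with equal shares.** With the same denominators and a true RR of 0.50:

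| True rates, expectant v ECC | All counted | 80% counted | 60% counted |
|---|---|---|---|
| 30% v 15% | 0.54 | 0.44 | 0.34 |
| 15% v 7.5% | 0.29 | 0.24 | 0.19 |

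Power is low even with complete counting, and the laser condition lowers it further.

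**The case against.** The strongest reply has four parts.

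- **No evidence of other treatments.** Nothing in the article says that retinopathy is treated other than by laser. This stands as a limit: the size of the loss cannot be estimated from the document, and if laser were the only treatment used the loss would be nil.
- **Condensed article.** The row may be shorthand, with the full protocol or case report form counting any treated disease. This carries less weight here. The row is not silent on the matter; it states a condition, in a table presented as a full description. If the fuller documents already count any treatment, the published wording should say so.
- **The imprecision swamps the effect.** On the illustrative figures the interval already runs from 0.23 to 1.91, so a shift to 0.89 would change no conclusion from this row alone. That is fair, and it is why the point is minor.
- **Core outcome set.** The article says that all core outcomes for preterm birth are included, and the row might follow a definition from that source. This cannot be checked here. Keeping the laser-only count as a sub-row protects against it.

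A reader might also infer that every baby with eye disease and no laser is wrongly missed. The document does not support that. Mild disease that needs no treatment is left out by a treatment threshold on purpose; the gap is confined to disease that was treated another way.

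**Conclusion.** The point holds in a narrow form. As worded, the retinopathy row leaves out babies whose disease needed treatment but was treated without laser. The supported consequence is a loss of scarce events and of precision in one secondary outcome, on the assumption that other treatments are used at all. The primary outcome, its analysis and the sample size of 260 are untouched.

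Two stronger conclusions are tempting and should not be drawn:

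- **That the comparison is biased.** The RRs of 0.89, 1.00 and 0.50 above appear only because the non-laser shares were set to differ twofold between the arms. ECC is meant to change gestation at birth and the trial is open, so a difference in treatment mode is possible, but nothing in the article shows one.
- **That neighbouring rows share the fault.** A reader might say that "Supplementary oxygen requirements at 36 weeks corrected gestational age" misses a baby on CPAP in air. That row names no lung disease and measures what it says, and CPAP is recorded under "Respiratory support (ventilation/CPAP)" and "Days on respiratory support", though not at 36 weeks. A reader might also say that "Confirmed sepsis (positive microbiology)" admits a colonised baby. The row requires sepsis and is paired with a clinically defined suspected-sepsis row; sample site and clinical criteria are details that a journal article can leave to the full protocol or case report form.

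**What to change.** Define the outcome as retinopathy of prematurity requiring any treatment (laser or other), and keep the laser-only count as a sub-row. The case report form should record whether any treatment was given and of what kind.

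The change adds no tests and no participants, and does not touch clinical care. It has three costs:

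- a small change to the neonatal case report form;
- a check of babies already recorded, because recruitment is open and the two definitions should not be mixed;
- slightly less direct comparison with studies that used a laser-only definition, which the sub-row largely restores.

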**Paediatric outcomes**	
Death at greater than 28 days until 2 years	
At 2 years corrected age, outcomes obtained from questionnaires, which includes general health, PARCA-R questionnaire and an assessment of motor outcomes (further details given in the statistical analysis plan).	

### Sample size estimates

Published literature [1, 2] noted large effect sizes in favour of cervical cerclage. We accept these effect sizes are likely to be exaggerated due to methodological limitations of these studies and so have opted for a more conservative target difference of a 33% relative risk reduction from 60% pregnancy loss in the expectant management group to 40% in the ECC group. To detect this difference with 90% power (*α* = 0.05) we require 260 women in total (130 in each arm). Smaller differences are also likely to be clinically relevant. The pregnancy loss rate in the expectant management arm is uncertain; however, 260 women would still achieve high levels of power (≥ 80%) in scenarios where the event rate approaches high levels (Fig. 2).

**Fig. 2 Fig2:**
[figure not shown]
Power curves assuming 33% relative risk reduction and event rates of 50%, 60%, 70% and 80% in the expectant management arm

### Statistical analysis

A separate statistical analysis plan for the quantitative analysis of the C-STICH2 study will provide a detailed description of the planned statistical analyses. A brief outline is given below.

Pregnancy loss will be summarised by treatment arm using frequencies and percentages. A log-binomial model will be used to generate relative risks (and 95% confidence intervals (CI)), adjusting for the minimisation variables.

Secondary outcomes which are binary will be analysed as per the primary outcome. Continuous outcomes which are deemed to be normally distributed will be summarised using means and standard deviations and a linear model will be fitted to generate adjusted mean differences (and 95% CIs). Continuous outcomes which are not deemed to be normally distributed will be summarised using medians and interquartile ranges and unadjusted differences in medians will be produced with 95% CIs. Time to event data will be summarised using medians and interquartile ranges. A Cox regression model will be fitted to generate adjusted hazard ratios (and 95% CIs) and a Kaplan-Meier plot will be produced to assess the data visually. All analyses will be adjusted for the minimisation variables (where possible).

All analyses will be by intention to treat. Every attempt will be made to collect pregnancy outcome data on all women, and it is anticipated that missing data will be minimal. Women with missing primary outcome data will not be included in the first instance. Sensitivity analyses will be conducted to assess the impact of missing data. Subgroup analyses will be limited to gestational age at randomisation, cervical dilatation and use of adjuvant therapies.

### Health economics

The principal economic analysis will be based on the data collected within the trial and will relate only to the initial period of assessment and the principal outcome of the trial at 7 days. The results of the economic evaluation will be expressed in terms of major outcomes averted (MOA), where MOA represents a composite outcome based on miscarriage, termination of pregnancy, neonatal death and PTB.

A further analysis based on all data up to the infant reaching 2 years of corrected age will be carried out; the outcome of this second analysis will be based on the parent report and neurodevelopment at 2 years.

The economic evaluation will primarily take the perspective of the NHS and Personal Social Services (PSS) and as far as possible, depending on available data in the literature, will also be analysed from the societal perspective. Data will be collected prospectively on NHS resource from all participating centres for both arms of the trial and follow-up care. Unit costs from routine sources will be attached to resource use to estimate overall costs for each trial arm.

A bootstrapping approach will be used to calculate confidence intervals around the difference in mean costs. Initially, the base-case analysis for the within trial analysis will be framed in terms of cost-consequences, reporting data in a disaggregated manner on the incremental cost and the important consequences as assessed in the trial arms. An incremental economic analysis will be conducted on the primary outcome and other secondary outcomes. The results of these economic analyses will be presented using cost-effectiveness acceptability curves to reflect sampling variation and uncertainties in the appropriate threshold cost-effectiveness value. Simple and stochastic cost-effectiveness analyses will explore the robustness of the results to plausible variations in key assumptions and variations in the analytical methods used, and to consider the broader issue of the generalisability of the results.

### Trial management and oversight

The trial is registered with the ISRCTN registry - trial reference ISRCTN12981869.

The trial is funded by NIHR HTA (project number 16/151/01). The sponsor is Birmingham Women’s and Children’s NHS Foundation Trust. Neither the funder nor sponsor is involved in data collection or analysis.

The trial will be administered by a clinical trials unit with extensive experience. Data will be kept in accordance with General Data Protection Regulations 2018. Completed CRFs will be reviewed by the clinical trials unit and missing or ambiguous data queried. The sponsor will ensure data integrity through quality assurance processes and audit at participating sites.

Any changes to the protocol will be agreed by the TSC prior to implementation and these will be disseminated to individual sites by the trial management group (TMG) subject to research ethics committee approval.

The TMG are responsible for the day to day running of the trial. The TSC and data monitoring committee (DMC) provide independent oversight of the trial including an assessment of the pilot study at the end of year two in line with the pre-specified objectives. TSC members include a majority of members who are independent of the investigators, their employers, institutions and the funding body. The DMC comprises three independent members (two obstetricians and a statistician with extensive trial experience) who are responsible for reviewing interim analyses. Responsibility for continuation or modification of the trial is held by the TSC and will include guidance from the DMC. The terms of reference and charter for this DMC will be guided by the DAMOCLES project, and we anticipate the DMC and TSC will meet biannually.

### Pilot evaluation

The internal pilot comprises the first 18 months of recruitment to C-STICH2. Following this, the feasibility of the trial will be assessed on its ability to screen, randomise and follow-up women. To support the quantitative assessment of feasibility a qualitative process evaluation is fully embedded in this pilot phase and will explore the feasibility, acceptability and appropriateness of the trial and intervention for HCPs and women (as described previously).

We have limited the use of fixed stop/go criteria for the pilot aiming to evaluate the strengths and weaknesses of the proposed trial qualitatively proposing solutions to the challenges experienced. This is partly because so little is known about the prevalence of the condition and its sequelae. Further information will be obtained from the minimal dataset.

Following the pilot phase of the trial the TMG and oversight committees will review the study progress and make recommendations to the funder on how the project should proceed. We anticipate multiple possible scenarios for how the project could proceed following the internal pilot, whilst maintaining the central research question. These are as follows:
The RCT is deemed feasible and remains unchanged (as detailed previously).The RCT is deemed semi-feasible, and a change is required. Recruitment is considered feasible; however, recruitment rates are not as anticipated and it is considered unlikely we will reach the original sample size target of 260 women within the propose timelines. Thus, the RCT could be potentially underpowered within the original sample size parameters. Alternative analysis methods will be considered. In this scenario, a prospective observational cohort study (POS) would be implemented to run in parallel to the trial, aiming to collect detailed information from eligible women who have declined participation in the randomised cohort or where the randomised trial was not offered to the women (Fig. 3A). Ineligible women or those who do not consent to the POS will be considered for the minimal dataset only (as per methods described previously). The POS data will aim to support findings from the RCT.The RCT is considered not feasible and is discontinued. In this scenario, the project would proceed with a POS and minimal dataset only (Fig. 3B).

**Fig. 3 Fig3:**
[figure not shown]
Scenarios for continuation of C-STICH2 if amendments required post pilot evaluation. **A** Scenarios for continuation of C-STICH2 (Option 2). **B** Scenarios for continuation of C-STICH2 (Option 3)

## Discussion

C-STICH2 is an RCT assessing the effectiveness of ECC in preventing pregnancy loss in mothers with cervical dilatation and exposed, unruptured membranes between 16 + 0 and 27 + 6 weeks of gestation. The situations where ECC may be considered are uncommon, including the absence of significant infection, heavy bleeding or active labour [18].

We anticipate that this trial will be challenging to run but, as indicated by NICE, it is important to provide evidence on which to base management decisions where ECC is potentially indicated. The presence of cervical dilatation and exposed membranes is frequently unanticipated by the woman and clinicians as symptoms may be mild without predisposing factors. Intervention with ECC is time critical in a situation where discussions about prognosis and survival of the woman’s foetus are needed. Recruitment to an ongoing RCT at such a time is distressing and adds further uncertainty for the woman and her family. Furthermore not all senior clinicians are competent or comfortable performing this procedure.

Thus there is a need for a robust RCT of ECC, with an RCT being the gold standard to determine the effectiveness of an intervention [5]. Observational data cannot demonstrate causality and are subject to confounding factors and bias [16]. The observational data already available are limited and at risk of bias [10]. The only completed RCT to date was too small and limited to inform practice [1].

C-STICH2 was designed to pro-actively address as many of these challenges as possible. The decision to leave eligibility primarily to the discretion of the senior clinician, as well as, peri-operative decision making and the use of any treatment adjuncts ensures the trial findings reflects clinical practice in this complex scenario. In addition, the trial facilitates professionals to work within the limits of their own equipoise in relation to the use of ECC. The internal pilot includes an embedded qualitative process evaluation and has clear objectives and scenarios for continuation. This will allow the TSC to consider the trial design and make amendments where appropriate to address any issues identified within the pilot. The minimal dataset will provide information on the prevalence of the condition and important outcomes which is important in understanding the natural history in women who are not eligible or decline randomisation. Each stage of the trial has been designed to be as pragmatic as possible, in order to maximise acceptability of the trial for clinicians and meet the needs of women participating.

In a trial of surgical intervention versus no intervention, it is not often possible to blind participants or HCPs to the intervention received. Whilst an open-label trial can potentially introduce bias, many of the outcomes and in particular the primary outcome (pregnancy loss) are objective and hence subject to less bias.

The qualitative process evaluation is key to this trial and will facilitate learning from the experiences of women and HCPs such that improvements can be made to improve care provision for these women. Findings of the qualitative study will allow the trial team to address barriers to participation where identified, build on facilitators, promote examples of good practice and explore concerns of both participants and HCPs. These will feedback into the design and conduct of the trial moving forward through the pilot period and into the full trial (Fig. 4).

**Fig. 4 Fig4:**
[figure not shown]
SPIRIT figure

## Patient and public involvement

Patients and patient groups are key to this programme being successful. They have been involved in developing the C-STICH2 trial protocol which included informing the choice of primary outcome and advising on the acceptability of trial processes. We have one patient co-applicant and two service user representatives. Our patient representative has direct experience of cervical cerclage and supports others through cerclage and second trimester pregnancy loss. Our two service user representatives, one from Tommy’s and one from the Miscarriage Association, have extensive experience of working with women and their families who have experienced miscarriage and/or PTB and so are ideally placed to support C-STICH2. Our patient representative sits on the TMG and our Miscarriage Association and Tommy’s representatives sit on the TSC providing important stakeholder oversight into trial management and decision making. Throughout the duration of the trial, our patient representative will continue to provide important insight into participant perspectives; support the development of all participant facing materials; contribute to data collection, analysis and interpretation of the qualitative process evaluation data; help to identify and overcome trial issues, and ensure appropriate dissemination of the findings of the study to women, their families and policymakers.

## Trial status

C-STICH2 opened to recruitment on the 1st February 2019. The pilot study is due to complete in August 2020 following which the TSC will make their recommendation. The full trial is expected to recruit for a further 2 years, with 2 years for follow-up therefore completing August 2024. Upon completion of the trial, findings will be disseminated to participants and published in a peer-reviewed journal.

This article is based on the current protocol V3.0; 31.01.2020.

